### Final diagnosis

The final diagnosis will be made based on GP’s medical records, including all letters from hospitals. All cases will be reviewed by an independent endpoint committee consisting of a cardiologist and GP for adjudication of the final diagnosis and the occurrence of MACE. The committee will be blinded for the randomisation and hs-cTnI on presentation. In case of disagreement, a second cardiologist will be consulted. The final diagnosis will be classified as ACS, stable coronary artery disease, cardiac but non-coronary disease, non-cardiac chest pain or death. ACS comprises myocardial infarction (ST-segment elevation myocardial infarction (STEMI) and non-STEMI (NSTEMI)) and unstable angina pectoris. Myocardial infarction is defined conform the fourth universal definition of myocardial infarction.^33^

A coronary angiogram (CAG) is the golden standard to establish the presence of coronary artery disease. However, CAG is costly and not without risk (eg, bleeding in approximately 7% and procedure-related myocardial infarction in approximately 6% of patients undergoing CAG).^34 35^ Therefore, we consider it too invasive and essentially unethical to perform a CAG in each patient in this relatively low-risk population. Hence, we will use a delayed reference standard, defined as ACS and MACE at the index consultation, within 6 weeks and 6 months after inclusion, to determine the diagnostic accuracy of the decision rule. The delayed reference method has been reported as a valid alternative if a golden standard test is too invasive and the disease is not self-limiting.^36^ This method has been used in similar studies before.^7 20 32 37^

### Secondary endpoints

Secondary endpoints are the cost-effectiveness of the clinical decision rule, adherence to the recommendations of the clinical decision rule by GPs, the patient’s reassurance, the diagnostic accuracy of the GP’s gut feeling and the diagnostic accuracy of the HEART (History, ECG, Age, Risk factors and Troponin) score for all patients with an ECG available (box 1).^31^ Finally, subgroup analyses for the primary endpoints will be performed for sex, region, socioeconomic status and duration of symptoms.

Box 1Secondary outcome measuresCost-effectiveness, consisting of a trial-based cost analysis and a cost–utility analysis (costs per quality-adjusted life year (QALY), assessed using the EQ-5D-5L questionnaire).^39 40^Adherence to the recommendations of the clinical decision rule by the general practitioner (GP), by comparing the GP’s policy with the recommendations of the decision rule.Reassurance of patients, using the State-Trait Anxiety Inventory after the index consultation.^41^Diagnostic accuracy of the GP’s gut feeling, by comparing the result of the gut feeling questionnaire with the occurrence of major adverse cardiac event (MACE) within 6 weeks after the index consultation.^42 43^Diagnostic accuracy of the HEART (History, ECG, Age, Risk factors and Troponin) score for all patients with an ECG available for the occurrence of MACE within 6 weeks after the index consultation.^31^Subgroup analysis for the primary outcomes for sex, region, socioeconomic status (using postal code) and duration of symptoms.

The cost-effectiveness of the clinical decision rule will be assessed alongside the trial. The analysis will be performed from a societal perspective. The costs are divided into healthcare costs and non-healthcare costs. Healthcare costs include those of the intervention and other healthcare use during follow-up. The costs of the clinical decision rule will be based on microcosting including the duration of the GP consultation, medical equipment and materials used. Healthcare use will be assessed by questionnaires at 6 weeks and 6 months follow-up. In this questionnaires, patients will be asked to fill out their total healthcare utilisation, such as GP visits, outpatient clinic visits, ED visits and hospital admissions for any reason. Reference prices published in the Dutch costing manual will be used to value healthcare use.^38^ To calculate non-healthcare costs, patients will be asked to note absence from paid and unpaid work. Productivity costs will be calculated using the friction cost method. Quality-adjusted life years (QALYs) will be calculated from utility scores from the EQ-5D-5L questionnaire administered at baseline, 6 weeks and 6 months follow-up.^39 40^ Finally, costs and QALYs between the control and intervention groups will be compared.

To assess the GP’s adherence to the recommendations of the decision rule, the outcome of the decision rule will be compared with the GP’s policy as reported by the GP. To assess the effect of the clinical decision rule on patients’ reassurance, patients will be asked to fill out the State-Trait Anxiety Inventory after the index consultation.^41^ To evaluate the diagnostic accuracy of the GP’s gut feeling, GPs will be asked to estimate the likelihood of ACS using the gut feeling questionnaire directly after the index consultation.^42 43^ The outcome of this questionnaire will be compared with the occurrence of MACE within 6 weeks. In all patients with an ECG, the HEART score will be scored retrospectively based on the information on the inclusion form filled out by the GP. The outcome will be compared with the occurrence of MACE within 6 weeks.^31^

### Sample size calculation

In primary care in the Netherlands, the reported hospital referral rate of patients with chest pain ranges from approximately 40%–70%.^1 6^ Similarly, a Swiss and Swedish study found referral and diagnostic testing rates of 59% and 43%, respectively.^44 45^ Based on these referral rates, we conservatively assumed a hospital referral rate of 40%. For the primary endpoint, we estimated a 10% decrease in referrals, resulting in 30% referrals, which is in line with a previous study estimating a 10% decrease in referrals when using the MHS.^45 46^ Group sample sizes of 448 (control group) and 896 (intervention group) achieve 80% power to detect the difference of 10% between both groups with a significance level (alpha) of 0.05 using a two-sided Z-test.^47^ The sample size is adjusted for a clustering effect with an intraclass correlation coefficient of 0.05 and for 1:2 randomisation.^48^ The estimated sample size needed is 500 for the control group and 1000 for the intervention group, accounting for a 10% lost to follow-up.

### Statistical analysis

Data will be analysed according to the intention-to-treat principle. Continuous demographic and baseline characteristics will be expressed as mean±SD and compared using the unpaired Student’s t-test. Categorical demographic and baseline characteristics will be described as frequencies and percentages and compared using the χ^2^ or Fisher’s exact test. The number of referrals will be presented as percentages and compared using the χ^2^ or Fisher’s exact test. To assess the diagnostic accuracy of the decision rule, sensitivity, specificity and predictive values will be calculated. The overall diagnostic accuracy will be assessed by means of the C-statistics. Missingness will be assessed, and if the percentage of missingness is >10%, multiple imputation will be applied. All analyses will be corrected for the correlation within clusters (general practices), using generalised estimating equations. Subgroup analyses will be performed for sex, region, socioeconomic status and duration of symptoms to confirm the applicability of the decision rule for different subgroups.

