## Methods and analysis

### Study design

The POB HELP study is a clustered diagnostic RCT. The study will be conducted in general practices in three regions in the Netherlands (Leiden, Maastricht and Venlo). General practices will be randomised to the intervention or control group in a 2:1 ratio. Randomisation is stratified for the three regions to ensure even distribution of rural and urban areas. Randomisation is done by Castor Electronic Data Capture using a variable block randomisation method.^18^ Patient inclusion started on 18 August 2021 and the study is planned to end on 1 July 2024.

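### The protocol names two different tests for the referral endpoint, χ²/Fisher and GEE, and does not say which gives the primary p-value; χ² would be anti-conservative if reported uncorrected

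*Protocol article*

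**What the plan says.** All references are to the Methods and analysis part of the protocol article.

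- **Study design.** Practices, not patients, are allocated 2:1 to the decision rule or regular care. "Randomisation is stratified for the three regions to ensure even distribution of rural and urban areas".
- **Primary endpoints.** The first of two is the hospital referral rate for acute chest pain.
- **Sample size calculation.** The control referral rate is taken as 40%, and "we estimated a 10% decrease in referrals, resulting in 30% referrals". The sizes, 448 control and 896 intervention, are said to "achieve 80% power to detect the difference of 10% between both groups with a significance level (alpha) of 0.05 using a two-sided Z-test". On clustering: "The sample size is adjusted for a clustering effect with an intraclass correlation coefficient of 0.05 and for 1:2 randomisation". Average practice size is not given.
- **Statistical analysis, on referrals.** "The number of referrals will be presented as percentages and compared using the χ^2^ or Fisher’s exact test".
- **Statistical analysis, later in the same paragraph.** "All analyses will be corrected for the correlation within clusters (general practices), using generalised estimating equations". Region appears in this section only as a subgroup variable.

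**The concern.** χ² and Fisher's exact tests treat every patient as independent. Patients of one practice share GPs and referral habits, and the whole practice is in one arm, so the variance of the difference between arms is larger than these tests assume.

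The GEE sentence does not settle the matter. A GEE analysis is a regression with its own Wald or score test of the arm effect. It is not an adjustment applied to a χ² statistic, and Fisher's exact test has no GEE form. A reader following the referral sentence and a reader following the GEE sentence would compute different p-values.

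At stake is which p-value decides a primary endpoint. With both on record the choice could be made after the data are seen, and one of the two is anti-conservative. This concerns what the text states. It is not a detail that an article may leave to an analysis plan: an unseen plan could resolve the conflict, but the published wording would still carry it.

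**Working it through.** **Inputs.** From Sample size calculation: 40% versus 30%, two-sided α 0.05, power 80%, allocation 1:2, ICC 0.05, 448/896 before loss to follow-up, 10% loss. Not stated: average practice size m, and its variation.

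**1. The protocol's own figures.** Control-arm size without clustering, with an intervention arm twice as large:

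- Unpooled: (1.96 + 0.842)² × (0.40×0.60 + 0.30×0.70/2) / 0.10² = 7.849 × 0.345 / 0.01 ≈ 271.
- Pooled under the null (mean rate 1/3): [1.96 × √(0.2222 × 1.5) + 0.842 × √0.345]² / 0.01 ≈ 265.
- Pooled with continuity correction: 280.

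With m unstated, 448 cannot be reproduced forwards. It can be back-solved from DE = 448/n and m = 1 + (DE − 1)/0.05:

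| Formula | n control | DE | Implied m |
|---|---|---|---|
| Continuity-corrected | 280 | 1.60 | 13.0 |
| Unpooled | 271 | 1.65 | 14.1 |
| Pooled | 265 | 1.69 | 14.8 |

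So 448/896 is consistent with about 13 to 15 patients per practice. The loss step agrees: 448/0.9 = 498 and 896/0.9 = 996, stated as 500 and 1000. No calculation error is shown.

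**2. Type I error if χ² is reported uncorrected.** Under the null, the naive statistic has variance DE instead of 1, so the error is 2 × [1 − Φ(1.96/√DE)].

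| Basis | DE | Type I error |
|---|---|---|
| Implied by 448/896, lowest | 1.60 | 12.1% |
| Implied, middle | 1.65 | 12.8% |
| Implied, highest | 1.69 | 13.2% |
| Assumed m = 10 | 1.45 | 10.4% |
| Assumed m = 20 | 1.95 | 16.0% |
| Assumed m = 30 | 2.45 | 21.0% |

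**3. Check by simulation.** Beta-binomial data, ICC 0.05, the same 40% referral rate in both arms, twice as many intervention practices, 20,000 runs:

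- m = 15, equal practices: 13.4% (formula 13.3%).
- m = 20, equal practices: 15.9% (formula 16.0%).
- Mean 15, with practice sizes Poisson around expected sizes with an assumed coefficient of variation of 0.5: 15.2%. At an assumed 0.8: 18.6%.

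A separate run of 4,000 trials with 32 and 64 practices of 14 gave 12.2% for χ² and 5.6% for a cluster-robust analysis.

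**4. What this means for one result.** To hold a true 5%, the naive test would need |z| > 1.96 × √DE. This is 2.48 (p below about 0.013) at DE 1.60, and 2.55 (p below about 0.011) at DE 1.69. A χ² p-value between roughly 0.011–0.013 and 0.05 would count as significant by the referral sentence, but would not hold up once clustering is allowed for.

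**5. Region.** Leaving a stratification factor out of the model keeps between-region variation in the error term. The standard error is then usually too large, which is conservative, so this does not feed into the figures above. The gain from including region depends on how much of the between-practice variance it explains, which the documents do not say. As an illustration only, assume 10–50% at m = 14. The ICC falls to 0.045–0.025, DE becomes 1 + 13 × 0.045 = 1.585 down to 1 + 13 × 0.025 = 1.325, and power rises from about 80% to about 82–88% (unpooled Z).

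**The case against.** The best defence is that the paragraph should be read as a whole. The GEE sentence covers every analysis, and the sample size already allows for an ICC of 0.05. On this reading χ²/Fisher names the kind of comparison for a binary outcome, and the general rule then makes it a clustered one. A GEE Wald or score test is itself referred to a χ² distribution, so the wording is loose but not fatal. Investigators who follow the whole paragraph get roughly 5%, as the 5.6% for the cluster-robust analysis suggests.

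Most of this stands. A reader might infer that the plan ignores clustering, or that its false-positive rate is 12–16%. The documents do not support either: a correction is stated, and the inflated rate belongs to an analysis that the GEE sentence rules out. The upper end also needs assumed practice sizes.

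The defence does not remove the contradiction. Fisher's exact test cannot be read as a GEE test, and the referral sentence names specific tests without making them descriptive.

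On region, the objection is that covariate lists are commonly left to an analysis plan, that the article does not exclude region from the model, and that 80% is already the planned power. That is right as far as calling it an error goes; region belongs here only as an inexpensive improvement. The small-sample correction and the effect scale are likewise matters for the analysis plan.

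**Conclusion.** The point holds as a stated contradiction about the primary p-value of the first primary endpoint. It does not hold as a finding that clustering is ignored.

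The size is conditional on the χ² test being reported uncorrected: about 12–13% type I error at the ICC of 0.05 and the design effect of 1.60–1.69 implied by 448/896. It is about 15–16% with an assumed average of 20 patients per practice or assumed moderate inequality in practice size, and higher under more extreme assumptions. Average practice size is inferred throughout.

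The missing region term is a separate and lesser matter. It costs precision by an amount the documents do not determine, and it contributes nothing to the inflation.

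**What to change.** In the Statistical analysis section:

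1. Delete χ²/Fisher for the referral comparison, or label it as descriptive and without a confirmatory p-value.
2. Name one primary analysis for referrals: a binomial GEE with general practice as the cluster and robust standard errors, with the test of the arm term giving the primary p-value.
3. Include region as a fixed effect, because randomisation was stratified on it.

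Link function, working correlation, effect scale and any small-sample correction can stay in the analysis plan. The cost is about two sentences of wording. No new data are needed: practice and region are already known from the randomisation. The wording should be settled before the outcome data are compared by arm.

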## Introduction

Chest pain is a common reason for consultation in primary care.^1 2^ In 4%–7% of patients presenting with chest pain, the pain is caused by acute coronary syndrome (ACS).^1–3^ Early identification and treatment of patients with ACS are important to avoid cardiac morbidity and mortality.^4^ However, it is challenging for general practitioners (GPs) to distinguish ACS from other—less acute and life-threatening—causes of chest pain, as they have to rely on symptoms and clinical signs only.^5^ Consequently, GPs refer approximately 40%–70% of patients presenting with chest pain to the hospital for further examination.^1 6^

Following referral, only 10%–20% of the patients are diagnosed with ACS.^7–9^ The relatively high number of referrals puts a high burden on patients and may lead to potentially avoidable adverse patient outcomes due to the risks associated with (unnecessary) diagnostic tests and overcrowding of emergency departments (ED).^10–12^ In addition, a high referral rate puts a lot of pressure on the healthcare system. Finally, evaluation of patients in the ED is costly, which has a significant impact on society as well.^13^ Therefore, measures to improve the referral efficiency of patients with acute chest pain are crucial.

A clinical decision rule may help GPs to safely rule out ACS and reduce hospital referrals. Previous studies in ED settings showed that a single high-sensitive cardiac troponin-I (hs-cTnI) measurement with or without a risk score is safe and effective to rule out ACS.^7 9 14^ However, due to the low incidence of ACS in primary care, results from ED settings are not generalisable to primary care settings. Although use of a troponin point of care test (POCT) in primary care reduced the number of referrals in both a model-based and an observational study, the impact has yet to be studied in clinical practice.^15–17^

Therefore, this clustered randomised controlled trial (RCT) aims to evaluate the impact of a primary care decision rule for acute chest pain, consisting of a risk stratification score combined with a hs-cTnI-POCT on the number of hospital referrals, and to assess its diagnostic accuracy. In addition, secondary endpoints including cost-effectiveness will be assessed.

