### Primary endpoints

The study has two primary endpoints. The first primary endpoint is the hospital referral rate for acute chest pain within 24 hours and 6 weeks after inclusion. The second primary endpoint is the diagnostic accuracy of the clinical decision rule. To study the diagnostic accuracy (ie, sensitivity, negative predictive value), the incidence of ACS and major adverse cardiac events (MACE) at the index consultation, within 6 weeks and 6 months after inclusion will be assessed. MACE is defined as a combined endpoint of ACS, percutaneous coronary intervention, coronary artery bypass grafting, coronary angiography revealing procedurally correctable stenosis managed conservatively and all-cause mortality.^7 31 32^

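### Diagnostic accuracy is a primary endpoint, but the sample size rests on referrals only and the prescribed GEE gives no valid interval for sensitivity or NPV if no case is missed

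*Protocol article*

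**What the plan says.** Under Primary endpoints the article states that "The study has two primary endpoints". The first is the referral rate. On the other it says: "The second primary endpoint is the diagnostic accuracy of the clinical decision rule", naming sensitivity and negative predictive value (NPV). The reference standard is "the incidence of ACS and major adverse cardiac events (MACE) at the index consultation, within 6 weeks and 6 months after inclusion".

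The Sample size calculation refers to one primary endpoint only: "For the primary endpoint, we estimated a 10% decrease in referrals, resulting in 30% referrals". The totals of 448 and 896 evaluable patients (500 and 1000 planned) follow from that comparison. No case number or precision is given for accuracy.

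Under Statistical analysis the article says "To assess the diagnostic accuracy of the decision rule, sensitivity, specificity and predictive values will be calculated", adds the C-statistic, and then sets one rule for clustering: "All analyses will be corrected for the correlation within clusters (general practices), using generalised estimating equations". It names no other interval method for the accuracy measures.

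Under Regular care and Intervention, only intervention practices use the Marburg Heart Score with the troponin point-of-care test. Control practices follow standard care.

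**The concern.** Sensitivity and NPV depend on how many cases the rule misses, and a rule-out strategy aims for none. GEE estimates a proportion on a model scale and takes its standard error from the variation observed between practices. If every case is detected there is no variation, so the method has nothing from which to build an interval. The prescribed analysis would therefore fail in the result the trial hopes for.

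The output in that case may also mislead. A printed interval of 100% to 100% looks like certainty, although a few dozen cases leave several percentage points of doubt. Because the sample size was set for referrals alone, nothing in the article warns the reader how few cases will support the second primary endpoint.

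**Working it through.** **Reproducing the stated sample size.** Inputs from the Sample size calculation: 40% v 30%, two-sided alpha 0.05, power 80%, allocation 1:2, ICC 0.05, 10% loss. The cluster size m is not stated; m = 14 is an assumption that recovers the published figure.
- Control n (unpooled) = (1.96 + 0.842)² × (0.40 × 0.60 + 0.30 × 0.70 / 2) / 0.10² ≈ 271.
- Design effect = 1 + (14 − 1) × 0.05 = 1.65, and 271 × 1.65 = 447.2, so 448 control and 896 intervention.
- Loss: 448 / 0.9 = 498 and 896 / 0.9 = 996, rounded to 500 and 1000.

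The figures reproduce, and no accuracy input enters them.

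**Expected cases in the intervention arm.**
- Introduction, 4–7% ACS: 896 × 0.04 = 36 and 896 × 0.07 = 63.
- Cross-check: the Introduction also says "Following referral, only 10%–20% of the patients are diagnosed with ACS". With the assumed 40% referral, 0.40 × 10–20% = 4–8%, or 36–72 cases.
- Upper assumption: 70% referred × 20% = 14%, about 126 cases.

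**Chance that no case is missed** = Seⁿ for true sensitivity Se and n cases.

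| Cases | Se 98% | Se 99% |
|---|---|---|
| 36 | 48% | 70% |
| 63 | 28% | 53% |
| 126 | 8% | 28% |

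**What GEE returns with no missed case.** Intercept-only binomial GEE was run on 36 and 63 cases over an assumed 30 practices. With a logit link the intercept ran off to about 25.6–26.6 and the interval printed as [1, 1]. With an identity link the standard error was 0 (independence) or the fit did not converge (exchangeable). The same applies to NPV, since no missed case means NPV = 100%.

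**What an exact interval returns.** With no missed case the two-sided 95% Clopper-Pearson lower limit is 0.025^(1/n).
- No missed case: 90.3% (n = 36), 94.3% (n = 63), 97.1% (n = 126).
- One missed: 85.5% (35 of 36), 91.5% (62 of 63).

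**How far clustering matters for sensitivity.** With an assumed 30 practices, 63 cases are 2.1 per practice. Applying the ICC of 0.05, the design effect is 1 + 1.1 × 0.05 = 1.055, so 63 / 1.055 ≈ 59.7 effective cases. The lower limit becomes 0.025^(1/59.7) ≈ 94.0%, against 94.3% unadjusted. Losing the GEE correction costs little here.

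**The case against.** The strongest reply is that this is a condensed article, that interval methods usually sit in the full protocol or analysis plan, and that the GEE sentence does not spell out a logit model for sensitivity. That disposes of some complaints: the absence of a minimum acceptable sensitivity, or of a fuller definition of a negative result, is not a finding here. It does not dispose of this one, because the article states a method for all analyses, and the logit and identity links tried both fail at the boundary.

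Other replies also limit the point:
- The failure is conditional. Specificity and PPV do not depend on missed cases in this way, and sensitivity and NPV can be estimated once a case is missed.
- The case number may exceed 36–63. The 4–7% refers to all chest pain, whereas enrolment needs GP suspicion of ACS (though highly suspicious telephone callers are excluded), and MACE to 6 months adds events. At 126 cases the failure is less likely but still possible.
- A reader might infer that GEE intervals are too narrow, and so flatter the rule, whenever few cases are missed. The calculations do not support this. At 35 of 36 the ordinary logit lower limit is 82.7% (ln 35 = 3.555, SE = √(1/35 + 1) = 1.014), below the exact 85.5%. Where coverage falls short, the upper limit is too low (2 missed of 36: upper limit 98.6%), which understates the rule.
- A reader might also infer that the safety claim rests on NPV alone, which is already 93–96% for an uninformative test at 4–7% prevalence. The article names sensitivity first and adds specificity and the C-statistic.
- Cases per practice cannot be stated as fact, since neither the number of practices nor the cluster size is given.

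**Conclusion.** The point holds in a limited form. One of two primary endpoints has no part in the sample size, and the method prescribed for it gives no valid interval for sensitivity or NPV when no case is missed. With 36–63 ACS cases this has a probability of 48–28% at a true sensitivity of 98% and 70–53% at 99%; with an assumed 126 cases, 8% and 28%. The uncertainty hidden in that event is material: exact lower limits are 90.3–94.3% for 36–63 cases.

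This rests on 896 evaluable intervention patients, the article's own prevalence range, ACS alone as the target condition, and independent detection across cases. It does not show that GEE is unsuitable for the other analyses, or that the accuracy endpoint was left unsized in documents not shown.

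**What to change.** In Statistical analysis:
- Keep GEE, or another cluster-adjusted method, for between-arm comparisons, specificity and PPV. Plain exact or Wilson intervals there would drop a correction that works: at the assumed design effect of 1.65 they would be about 22% too narrow (1 − 1/√1.65 = 0.22).
- For sensitivity and NPV, prespecify an interval that is valid at the boundary (Clopper-Pearson or Wilson), with a cluster-adjusted effective sample size where a design effect can be estimated.
- Do not rely on a practice-level bootstrap when no case is missed, because every resample then returns 100%.
- For the C-statistic, use a cluster-aware non-parametric variance.

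In Sample size calculation, say that the total rests on the referral endpoint only. Add that, with 0–1 missed of 36–63 cases, the exact 95% lower limit for sensitivity will be about 85–94%.

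The cost is a few sentences, slightly more analysis work, and a published precision less favourable than readers may expect. No extra patients are needed and clinical management does not change.

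### The subgroup analyses are given a confirmatory purpose that a trial sized for one overall referral contrast cannot deliver

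*Protocol article*

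**What the plan says.** In the Protocol article, Statistical analysis ends with the purpose of the subgroup work: "Subgroup analyses will be performed for sex, region, socioeconomic status and duration of symptoms to confirm the applicability of the decision rule for different subgroups". The Secondary endpoints section fixes the scope and rank: "subgroup analyses for the primary endpoints will be performed for sex, region, socioeconomic status and duration of symptoms". Box 1 there lists the same analyses as a secondary outcome measure.

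The primary endpoints differ in kind. One is a between-arm comparison: "The first primary endpoint is the hospital referral rate for acute chest pain within 24 hours and 6 weeks after inclusion". The other is a property of the rule itself: "The second primary endpoint is the diagnostic accuracy of the clinical decision rule".

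The Sample size calculation covers one overall referral contrast. It starts from 40% ("we conservatively assumed a hospital referral rate of 40" per cent), expects 30% with the rule, and states that 448 control and 896 intervention patients "achieve 80% power to detect the difference of 10% between both groups with a significance level (alpha) of 0.05 using a two-sided Z-test". It uses an intraclass correlation of 0.05 and 1:2 allocation. No subgroup calculation is given.

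**The concern.** Confirming that the rule applies in a subgroup is a positive claim about that subgroup, and it needs enough information there. The trial is sized to reach 80% power once, with everyone included. A subgroup result then invites two misreadings. A uniform reduction in referrals can look absent in one region or one sex, and a handful of ACS cases without a miss can look like proof of safety.

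The second matters most for duration of symptoms. The Safety section itself calls the evidence for presentation 1 to 3 hours after onset inconclusive, and the Abstract foresees separate papers on subgroup analyses. A result published there as confirmation would carry more weight than the data can bear.

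**Working it through.** **Inputs from the article.** Referral 40% vs 30%; two-sided alpha 0.05; 80% power; allocation 1:2; ICC 0.05; 448/896 evaluable; three regions; ACS in 4% to 7% of primary care chest pain (Introduction).

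**Assumptions.** Mean cluster size m (not given), equal subgroup sizes, and two levels each for socioeconomic status and duration of symptoms. Referral figures are for one referral window.

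**1. Reproducing the stated sample size.** The pooled rate is (0.40 + 2 × 0.30)/3 = 1/3.

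- Unclustered control group: n = [1.96 √(1/3 × 2/3 × 1.5) + 0.842 √(0.24 + 0.21/2)]² / 0.10² = 264.4, so 265. With continuity correction it is 280.
- Design effect: 1 + (m − 1) × 0.05. At m = 13, 280 × 1.60 = 448, the stated figure. At m = 15 without the correction, 265 × 1.70 = 450.5.
- Loss to follow-up: 448/0.9 = 498 and 896/0.9 = 996, in line with 500 and 1000.

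So m of about 13 to 15 fits the plan. Overall power (without continuity correction) is then 82% to 80%.

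**2. Referral power within subgroups, uniform 40% vs 30%.** Power = Φ[(0.10 − 1.96 s₀)/s₁], where s₀ = √(2/9 × 1.5/n), s₁ = √(0.24/n + 0.21/(2n)), and n is the effective control number.

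| Subgroup | Design effect | Effective control n | Power |
|---|---|---|---|
| Half, full design effect | 1.60 to 1.70 | 224/1.60 = 140 to 224/1.70 = 132 | 54% to 51% |
| Half, spread within practices (cluster size m/2) | 1.275 to 1.325 | 176 to 169 | 63% to 61% |
| One region of three (whole practices) | 1.60 to 1.70 | 93 to 88 | 39% to 37% |

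**3. If each level had its own 0.05 test and the effect were uniform.**

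- At least one sex not significant: 1 − 0.629² = 60% up to 1 − 0.511² = 74%.
- At least one region not significant: 1 − 0.389³ = 94% up to 1 − 0.370³ = 95%.
- A clustered simulation (30 and 60 practices of 15 patients, ICC 0.05, cluster-robust tests) agrees. Among trials with a significant overall result, all three regions are significant in about 7%.

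**4. The same rule under no effect.** With 9 levels (2 + 3 + 2 + 2), the simulation gives at least one nominally significant level in about 31% of trials in either direction, but only about 15% in favour of the decision rule. The bound for independent two-sided tests is 1 − 0.95⁹ = 37%.

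**5. Diagnostic accuracy.** Expected ACS cases are 896 × 0.04 = 36 to 896 × 0.07 = 63. That is about 18 to 31 in a half and 12 to 21 in a third. With k cases and none missed, the exact lower 95% limit for sensitivity is 0.025^(1/k).

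| Group | k | Lower 95% limit |
|---|---|---|
| All intervention patients | 36 to 63 | 90% to 94% |
| Half | 18 to 31 | 81% to 89% |
| Third | 12 to 21 | 74% to 84% |

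Enrolled patients are those in whom the GP suspects ACS, so incidence could exceed 7%. At 10%, taken only as an illustration, there are about 90 cases, 45 per half, and the limit is 0.025^(1/45) = 92%.

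**The case against.** The strongest reply is that one verb is being made to carry too much. Four stronger inferences should indeed be set aside.

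- **No ranking of the subgroups.** A reader might infer this from the purpose statement alone. The document contradicts it: the Secondary endpoints section and Box 1 place these analyses among the secondary ones, and the primary outcomes go to the main paper. That ranking limits their weight, but it does not make them exploratory.
- **A missing interaction test, multiplicity rule or exploratory label.** A condensed article commonly leaves these to the full protocol or SAP, which are not shown. Their absence is no fault here. They appear below only as part of the remedy.
- **A null effect will often look present somewhere.** This rests on testing each level at 0.05, which the article nowhere states; the analyses could equally be estimates checked for consistency. Even under that rule, the chance of a result that favours the rule is about 15%, because the 31% counts both directions.
- **One argument for both primary endpoints.** Diagnostic accuracy has no between-arm effect, so power and interaction reasoning fits referral only. For accuracy the issue is imprecision.

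What remains is the stated purpose. An unseen SAP could supply methods, but it could not make this sample size confirm applicability subgroup by subgroup.

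**Conclusion.** The point holds in a narrow form and is of modest severity. The article states a confirmatory purpose for subgroup analyses that the design cannot serve. Referral power falls from about 80% overall to 51% to 63% in a half and 37% to 39% in a region. Subgroup sensitivity would, even with a perfect result, remain compatible with missing roughly 11% to 19% of ACS cases in a half and 16% to 26% in a third.

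The region result needs only three roughly equal regions and a cluster size that fits the plan's own figure. The sex result needs a near-equal split. The nine-level figure also depends on assumed categories for socioeconomic status and duration. The sensitivity limits depend on the 4% to 7% incidence and would be tighter if more enrolled patients have ACS. The primary analysis and the sample size are not affected.

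**What to change.** In Statistical analysis, replace the confirmatory purpose with a statement that these secondary analyses explore whether results differ between subgroups. Then:

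- **Referral:** fit one arm-by-subgroup interaction term per factor in the GEE model already planned, and show the effect in each level with its 95% CI.
- **Accuracy:** report sensitivity and negative predictive value by subgroup descriptively, with exact 95% CIs.
- **Interpretation:** draw no claim of confirmed or absent applicability from a single subgroup.

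This costs a few sentences and four model terms, with no new data or patients. The interaction tests have limits of their own. For two equal halves the variance is 2 × [0.24/(n/2) + 0.21/n] with n = 448/design effect. At design effects of 1.60 to 1.27, power is about 30% to 36% for a 10-point difference in effect and 81% to 89% for a 20-point difference. A non-significant interaction is therefore not evidence of uniformity, which is a further reason for the exploratory wording. The price is giving up a confirmatory subgroup claim that the sample size does not support.
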